**Results:**

The primary objective of this study is to characterize the epidemiology of NARDS in this regional population and to test the following hypotheses: (1) The true incidence, etiology, and mortality rates of NARDS in Shenzhen will differ from existing international and Chinese cohorts, and these differences can be systematically explained by specific clinical and demographic factors. A multi-modal predictive model that integrates early clinical variables with multi-omics biomarkers has the potential to accurately identify neonates at high risk for severe NARDS [oxygenation index (OI) ≥ 16] and long-term adverse outcomes [Area Under the Receiver Operating Characteristic Curve (AUROC) > 0.85].

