### Biomarker and predictive modeling outcomes

4.3

The primary outcomes related to the multi-omics biomarker analysis are:
The identification and validation of a proteomic and/or metabolomic signature, derived from baseline (within 24 h of diagnosis) plasma/serum samples, that demonstrates high accuracy [defined as an Area Under the Receiver Operating Characteristic Curve (AUROC) > 0.85] for predicting the development of severe NARDS (OI ≥ 16) within 72 h of diagnosisThe discovery of novel genetic variants *via* a Genome-Wide Association Study (GWAS) that are significantly associated with susceptibility to NARDS and/or in-hospital mortality.

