### Machine learning and predictive modeling

6.2

Beyond conventional regression, predictive modeling will employ a suite of algorithms, including penalized logistic regression (Elastic Net), decision trees, random forests, gradient boosting machines, support vector machines, and artificial neural networks. Two primary prediction tasks will be addressed: Early identification of neonates at risk of severe NARDS (OI > 16 within 72 h of diagnosis); Long-term prognosis (mortality, NDI, SRM, or growth restriction at the 24- and 36-month corrected age). Candidate predictors will be selected based on clinical relevance and temporal availability (within 24 h for early warning models; within 7 days for prognostic models). Feature selection and regularization will primarily use Elastic Net. To identify novel NARDS endotypes, Integrative Multi-Omics Factor Analysis (MOFA) or similar unsupervised data integration approaches [e.g., sparse Partial Least Squares Discriminant Analysis (sPLS-DA)] will be employed to identify latent factors and co-varying molecular pathways across omics layers. These integrated molecular signatures will subsequently serve as input features for downstream machine learning models (e.g., Random Forest) to construct highly discriminative and biologically informed predictive classifiers.

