### Multi-omics integration and validation

6.4

Biomarker discovery will follow a split-sample design, with the cohort randomly divided into a training set (70%) and an independent validation set (30%). Within each omics layer, initial feature selection will be conducted using multivariate analytical techniques such as PLS-DA. Subsequently, integrative multi-omics analyses will be performed using the DIABLO framework (Data Integration Analysis for Biomarker Discovery using a Longitudinal Approach) to construct predictive models that integrate molecular and clinical data. Model performance will be evaluated in the validation set using AUROC, sensitivity, specificity, and calibration metrics, ensuring rigorous validation of biomarker-based classifiers.

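### AUROC > 0.85 is attached to two different models and outcome sets that are not labelled as separate criteria, and section 6.4 describes no evaluation of the omics signature named in 4.3

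*Protocol article*

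**What the plan says.** The cut-off of 0.85 is the only numeric performance target for a model in the protocol article. It appears in two places.

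- **Abstract, Results.** Among the hypotheses to be tested: "A multi-modal predictive model that integrates early clinical variables with multi-omics biomarkers has the potential to accurately identify neonates at high risk". The outcomes are severe NARDS (OI at or above 16, no time window) and "long-term adverse outcomes [Area Under the Receiver Operating Characteristic Curve (AUROC) > 0.85".
- **Section 4.3.** A primary outcome of the biomarker analysis: "The identification and validation of a proteomic and/or metabolomic signature, derived from baseline (within 24 h of diagnosis) plasma/serum samples, that demonstrates high accuracy", with high accuracy "defined as an Area Under the Receiver Operating Characteristic Curve (AUROC) > 0.85". The outcome is severe NARDS within 72 h of diagnosis. Neither clinical predictors nor long-term outcomes are named.

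The modelling sections set no pass mark. Section 6.2 lists two primary prediction tasks: "Early identification of neonates at risk of severe NARDS (OI > 16 within 72 h of diagnosis") and "Long-term prognosis (mortality, NDI, SRM, or growth restriction at the 24- and 36-month corrected age"). Section 6.4 selects features within each omics layer, then uses DIABLO "to construct predictive models that integrate molecular and clinical data", and evaluates model performance in a 30% validation set.

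**The concern.** The same number is used as a target for two objects that differ in predictors, outcomes and time window. Nothing says whether they are one criterion worded loosely or two criteria. The evaluation in 6.4 matches the abstract's model rather than the signature that 4.3 makes a primary outcome.

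What is at stake is the biomarker claim. Severe NARDS is defined by a cut-off on the oxygenation index. Table 1 in section 3.8 collects blood gases, respiratory support parameters and illness severity scores on day 1, and section 6.2 admits predictors available within 24 h to the early-warning models. Such variables could enter the combined model and carry much of its accuracy. An AUROC above 0.85 for that model would then say little about the proteomic or metabolomic data. The planned output would include no figure from which a reader could tell.

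**Working it through.** **The plan's own arithmetic.** The only sample size calculation (section 3.6.2) is for an in-hospital mortality model: 10 events × 10 predictors = 100 deaths; 100 / 0.126 = 793.65, rounded up to 794. It reproduces, but it does not use the AUROC target, which has no derivation to check. The check is therefore mainly a comparison of text.

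**Side by side.**

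| | Abstract | 4.3 | 6.2 | 6.4 |
|---|---|---|---|---|
| Predictors | Early clinical + multi-omics | Baseline plasma/serum proteomic and/or metabolomic | Clinical relevance and timing; integrated molecular signatures as inputs | Molecular + clinical |
| Outcome | Severe NARDS and long-term | Severe NARDS | Severe NARDS; long-term | Not stated |
| Window | None for severe NARDS | 72 h | 72 h; 24 and 36 months | Not stated |
| Target | > 0.85 | > 0.85 | None | None |

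The abstract and 4.3 share only the number and the severe NARDS outcome. If the bracket in the abstract is read as covering the long-term outcomes alone, they share only the number.

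**Can the two criteria disagree?** The AUROCs below are assumptions; the document gives none. Model: two normally distributed scores with equal variance in both outcome groups and correlation ρ between them.

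- Separation of one score: d = √2 × Φ⁻¹(AUROC). Clinical 0.82 gives d = 1.2945; omics 0.75 gives d = 0.9539.
- Best linear combination: D² = (d_c² + d_o² − 2ρ·d_c·d_o) / (1 − ρ²); combined AUROC = Φ(D/√2).
- d_c² + d_o² = 2.5857 and d_c·d_o = 1.2348.
- ρ = 0: D² = 2.5857, AUROC **0.872**.
- ρ = 0.2: D² = (2.5857 − 0.4939)/0.96 = 2.179, AUROC **0.852**.
- ρ = 0.3: D² = (2.5857 − 0.7409)/0.91 = 2.027, AUROC **0.843**.

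A second pair, clinical 0.84 and omics 0.70, gives 0.870, 0.853 and 0.847 at the same correlations. In both pairs the combined model passes at ρ of 0 and 0.2 while the signature sits 0.10 (0.85 − 0.75) or 0.15 (0.85 − 0.70) below the target. At ρ = 0.3 the combined model fails too. The disagreement is not inevitable even under independence: 0.80 with 0.70 combines to 0.839, and neither passes.

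The criteria can also disagree the other way. A 72 h signature above 0.85 would meet 4.3, while a long-term model at or below 0.85 would miss the abstract's target.

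**The case against.** The strongest reply is that the two statements do not contradict each other. One cut-off can apply to two models. Section 4.3 limits itself to the biomarker analysis, which draws on a voluntary sub-study with its own consent (section 3.8.2), while the abstract speaks only of potential. This stands in part: the two can coexist, and the textual defect is that they are not labelled as separate. The softer wording does not remove the issue, because the abstract lists the statement as a hypothesis to test and gives it a number.

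A reader might infer that one result could both meet and miss the target. It could not: a single model's AUROC for a single outcome lies on one side of 0.85. Only a set of results can split.

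A reader might also infer that 4.3 lets a model driven by oxygenation data count as a validated biomarker signature. Its wording does not allow that, since it asks for "The identification and validation of a proteomic and/or metabolomic signature, derived from baseline (within 24 h of diagnosis) plasma/serum samples". The risk comes from 6.4, where the integrated model is the one whose held-out AUROC will be available. Use of OI as a predictor is likewise not stated; it is a possibility inferred from what is collected on day 1.

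Finally, 6.4 does not exclude an omics-only evaluation, 6.2 feeds molecular factors into classifiers without saying whether clinical variables join them, and 6.3 covers model evaluation in general. A condensed article may leave model comparisons to the full plan, so the absence of a three-way comparison would not be a finding by itself. What remains is that the article states a primary outcome for one object and describes held-out evaluation for another.

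**Conclusion.** The concern holds as a mismatch between a stated target and the analysis described for it. AUROC > 0.85 governs two objects that are not identified as separate criteria, and 6.4 does not evaluate the signature that 4.3 names. A combined AUROC above 0.85 would leave the contribution of the biomarkers unknown.

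The numerical size is illustrative only. It rests on assumed AUROCs and a binormal model, and in both worked pairs the split between the two criteria is present at correlation 0.2 and gone at 0.3. Scores that reflect the same illness at the same time may well be correlated more strongly than that. The case for change therefore rests on the text, and the numbers show only that a split is possible.

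A reader might conclude that the long-term outcomes should lose their target or become exploratory. The document does not support that: section 2.2.2 makes long-term prognosis part of a secondary objective, and 6.2 names it as one of two primary prediction tasks.

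**What to change.** 1. Label the two criteria as separate. For each, state the model and its predictors, the outcome, the time window and the data set in which the AUROC is judged. Use the same wording in the abstract, 4.3 and 6.2 to 6.4. The severity cut-off must be reconciled at the same time: OI at or above 16 in the abstract, 3.6.1 and 4.3, but above 16 in 6.2.
2. In 6.4, judge the 4.3 criterion on the omics-only signature in the 30% held-out set.
3. In the same held-out infants, report clinical-only, omics-only and combined AUROCs. Base any claim of biomarker value on the combined-minus-clinical difference with its confidence interval.
4. Keep long-term prognosis as a stated prediction task.

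The cost is wording in these sections and a few extra model fits on data already planned. The biomarker claim may become less favourable, and precision will be limited. At the target of 1,000, the held-out set is at most 0.30 × 1,000 = 300 infants, and fewer to the extent that biobank consent is declined. If 20% of 300 were severe (60 infants, an assumption), an AUROC of 0.85 would have a standard error of about 0.032 (Hanley–McNeil) and a 95% interval of about 0.787 to 0.913.

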**Conclusions:**

The SZ-NARDS cohort is uniquely positioned to resolve a major clinical contradiction in NARDS epidemiology. By integrating deep phenotyping with a longitudinal biobank and advanced machine learning algorithms, this initiative will generate a comprehensive dataset. This dataset will serve to refine existing prognostic models, identify regional disparities in disease biology, and inform the development of precision medicine interventions for this vulnerable population.

**Clinical Trial Registration:**

Chinese Clinical Trial Registry, identifier ChiCTR2400093854.

## Introduction

1

Acute Respiratory Distress Syndrome (ARDS) was first described in 1967 as a severe respiratory condition characterized by reduced lung volumes, decreased lung compliance, and a significant ventilation-perfusion mismatch, ultimately leading to progressive hypoxemia and respiratory distress (1–3). ARDS affects individuals across all age groups, including adults (4), children (5), and neonates (6). However, the etiology, clinical presentation, treatment, and prognosis of neonatal ARDS (NARDS) differ significantly due to the unique developmental status of neonatal lungs and their immature immune function (7). Global data show that the mortality rate of NARDS is approximately 20% (8), and survivors often face long-term developmental impairments. This places a significant emotional and financial burden on families (9–12). These unique challenges highlight the critical importance of advancing research on NARDS.

The Montreux definition for NARDS, which was introduced in 2017, signified the initial phase of NARDS research, with a predominant focus on clinical and investigative purposes (6). Following the study protocol, the second phase of this project involves a prospective cohort study with two primary aims: first, to determine the prevalence of NARDS; and second, to characterize the epidemiology, clinical progression, treatment, and outcomes of neonates meeting the Montreux criteria. This methodological approach mirrors the processes followed after the establishment of the Berlin definition of ARDS for adults and the Pediatric Acute Lung Injury Consensus definitions for children (4, 13). However, it is noteworthy that no large-scale international NARDS registry has been established, with only two prospective cohort studies currently available. De Luca et al. (2022) (8) conducted the first international multicenter study, reporting a NARDS prevalence of 1.5% and a mortality rate of 17%–24%. They identified sepsis, aspiration syndromes, and pneumonia as the leading etiologies. Similarly, in 2023, Long Chen et al. (14) conducted a multicenter study in China, which reported a comparable prevalence (1.44%) but a strikingly lower mortality rate (12.6%), with pneumonia, asphyxia, and early-onset neonatal sepsis as the predominant causes. These findings underscore not only regional variations in NARDS prevalence, mortality, and etiological factors, but also reveal a critical clinical paradox: why does NARDS mortality in China appear significantly lower than the international average? Potential explanations for this discrepancy remain unexplored and may include: (1) differences in etiological distributions (e.g., a higher proportion of direct vs. indirect lung injury in Chinese cohorts); (2) variations in clinical management strategies (e.g., surfactant use, ventilation protocols); or (3) demographic factors (e.g., gestational age profiles, access to tertiary care). Resolving this contradiction is essential for refining our global understanding of NARDS pathophysiology and optimizing resource allocation. Nevertheless, a notable limitation in these studies was their emphasis on etiology and short-term outcomes, offering scant insight into the longer-term implications of the condition. To address these gaps, our study undertakes a 3-year, large-scale, multicenter cohort investigation. It will place particular emphasis on the long-term follow-up of patients at high risk of mortality and explicitly aim to dissect the drivers of the observed regional mortality disparity. This will offer a more comprehensive understanding of the natural history of NARDS, thereby expanding the current body of literature and providing mechanistic insights into how the Montreux definition applies across diverse healthcare settings.

Despite significant advancements in the definition and standardization of NARDS, critical challenges persist in accurately identifying severe cases and predicting clinical outcomes. The PaO_2_/FiO_2_ ratio, a cornerstone of the Berlin criteria for adult ARDS, has been shown to be suboptimal in the neonatal population due to its dependence on positive end-expiratory pressure (PEEP). Notably, studies have demonstrated that neonates requiring higher PEEP often display PaO_2_/FiO_2_ ratios comparable to those with milder lung injury, which can lead to diagnostic ambiguities and the potential for undertreatment in critical cases (15). The 2023 Pediatric Acute Lung Injury Consensus Conference (PALICC-2) criteria introduced severity-specific indices, such as PaO_2_/FiO_2_ or SpO_2_/FiO_2_ for mild cases and the oxygenation index (OI) or oxygen saturation index (OSI) for severe cases (16). However, neonatal-specific physiological factors, including the elevated oxygen affinity of fetal hemoglobin and circulatory variability in preterm infants, significantly undermine the reliability of these indices (17). The Montreux criteria represent an advancement by prioritizing the OI, which demonstrates a stronger correlation with morbidity and mortality (18). Nevertheless, their practical application in neonatal intensive care units (NICUs) is hindered by several constraints, including inconsistent access to arterial blood gas analysis and inaccuracies inherent in transcutaneous oxygen measurements in preterm neonates (19). Moreover, the Montreux criteria, predominantly derived from adult and pediatric ARDS data, lack a robust foundation of neonatal-specific evidence, thereby limiting their precision and generalizability. This issue is compounded by the substantial heterogeneity observed in NARDS, encompassing diverse etiologies, clinical trajectories, and treatment responses. Addressing these limitations necessitates large-scale, prospective studies aimed at refining diagnostic criteria and developing predictive models that are specifically tailored to the neonatal population.

The heterogeneity of NARDS presents another challenge in clinical practice, as no specific treatments have been approved, and current clinical trials have yet to generate sufficient evidence for evidence-based interventions. Biological samples, such as blood and tracheal aspirate, are critical for advancing our understanding of NARDS at the genetic and molecular levels. Embedding these samples into biobanks within registry systems can promote translational research, facilitating phenotypic analyses and personalized treatments for NARDS patients. Though translational research on ARDS in adults and children has made substantial progress (20–22), studies focused on NARDS remain limited (23–25). Expanding biobank initiatives globally, particularly in non-Western populations, is vital for capturing regional genetic and molecular variations that can inform clinical guidelines. Furthermore, modern computational tools like machine learning (ML) offer a powerful way to analyze biobank data, uncover novel patterns for risk stratification, and personalize treatment strategies (26, 27). In ARDS, ML-derived phenotypes and prediction rules hold promise for personalized care. Recent ARDS literature emphasizes that precision medicine approaches—guided by biomarkers and ML—can identify subgroups of patients likely to respond differently to therapies (28, 29). Leveraging insights into neonatal immune response and lung development, this study will utilize machine learning to construct prognostic models by integrating biomarkers with clinical variables unique to neonates, such as gestational age and perinatal risk factors. These underexplored parameters in existing ARDS prediction frameworks hold potential for enhancing diagnostic precision, optimizing clinical outcomes, and advancing personalized care for this highly vulnerable population.

The SZ-NARDS cohort study will formally be initiated in January 2025. This is the only large prospective, multicenter, open, longitudinal cohort study on NARDS in Shenzhen, China, a special economic zone city in China. The SZ-NARDS cohort study will recruit eligible individual NARDS patients and comprehensively collect their clinical data and specimens with longitudinal follow-up for future research. Herein, we describe the rationale and design of the SZ-NARDS registry.

## Objective

2

### Primary objective

2.1

The primary objective of the SZ-NARDS cohort study is to establish a prospective, multicenter registry to comprehensively characterize the epidemiology, clinical phenotypes, and short- and long-term outcomes of NARDS in a large, contemporary neonatal cohort within the Shenzhen region.

### Secondary objectives

2.2

The secondary objectives are grouped into three key areas of investigation:

#### Epidemiological and clinical characterization

2.2.1

To evaluate the prognostic performance and clinical utility of the Montreux NARDS definition within the Shenzhen cohort. This involves assessing its association with mortality, severe morbidity, and long-term neurodevelopmental impairment (NDI), thereby establishing a robust framework for subsequent deep phenotype analysis.To determine the incidence, disease burden, and clinical characteristics of NARDS in participating NICUs, and to describe the short-term mortality and morbidity of affected infants.To characterize the clinical trajectories of NARDS, including the time course from the inciting insult to key endpoints such as severe disease, the requirement for extracorporeal membrane oxygenation (ECMO), or death, and to analyze mortality patterns over a three-year follow-up period.

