**Figure 1 F1:**
[figure not shown]
Flow chart of the study design, the SZ-NARDS, 2025-2028. Neonates diagnosed with ARDS were enrolled as participants, with clinical measurements and biological specimens collected on day 1, during the acute exacerbation phase (defined by the peak OI), on day 28, and within 24 h before death or initiation of ECMO. Outcome data, including censored cases, will be finalized in 2028 after completing follow-up through clinic visits or phone calls. ARDS, acute respiratory distress syndrome; ECMO, extracorporeal membrane oxygenation; SZ-NARDS, the Shenzhen neonatal acute respiratory distress cohort study; OI, oxygenation index.

Clinical management of patients will remain at the discretion of the local attending physicians according to institutional guidelines, with no study-specific interventions. The study features an open design, allowing for the potential inclusion of additional centers that meet the established criteria during the recruitment period.

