#### Inclusion and exclusion criteria

3.6.1

Neonates will be enrolled consecutively upon meeting the full set of Montreux criteria for the diagnosis of NARDS during hospitalization. This cohort will include infants of all gestational ages, including premature infants, provided their respiratory distress meets all five Montreux criteria. These criteria include: (1) an acute onset of symptoms within one week following a known or suspected clinical insult; (2) exclusion of respiratory distress attributable to neonatal respiratory distress syndrome (NRDS), transient tachypnoea of the newborn (TTN), or congenital anomalies; (3) radiological evidence of bilateral, diffuse irregularities, including reduced translucency or opacities, that cannot be explained by conditions such as pleural effusion, atelectasis, NRDS, TTN, or congenital anomalies; (4) absence of congenital heart disease as the cause of pulmonary oedema, with echocardiographic confirmation required to verify the origin of the oedema; and (5) the presence of an oxygenation deficit, categorized by the OI as mild (4 ≤ OI < 8), moderate (8 ≤ OI < 16), or severe (OI ≥ 16). All five criteria must be fulfilled for diagnosis.

Exclusion criteria include: (1) respiratory distress due to primary surfactant deficiency (e.g., hyaline membrane disease), TTN, or congenital lung malformations; (2) congenital heart disease resulting in pulmonary oedema; (3) known genetic syndromes or chromosomal abnormalities; (4) data that did not conform to the Montreux criteria or cases with unavailable outcome data; and (5) abandonment or death occurring within 24 h of birth.

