### Statistical analysis plan

6.1

Continuous variables will be summarized as mean ± standard deviation (SD) or median with interquartile range (IQR), depending on distribution. Categorical variables will be presented as frequencies and percentages. Group comparisons will be conducted using the student's *t*-test or Mann–Whitney *U* test for continuous variables, and the *χ*² test or Fisher's exact test for categorical variables.

Univariate logistic regression will be used to examine associations between NARDS and study outcomes. Multivariable logistic regression will then be performed to identify independent predictors. Missing data will be addressed primarily using multiple imputation by chained equations (MICE), assuming data are missing at random. Variables with excessive missingness will be excluded according to predefined thresholds, and the imputation model will be structured accordingly. Sensitivity analyses will include complete-case analysis, k-nearest neighbors (k-NN) imputation, and inverse probability weighting to evaluate the robustness of findings to loss to follow-up. A two-sided *p* < 0.05 will be considered statistically significant. All analyses and visualizations will be conducted using R software (version 4.3.3).

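### The time-course and three-year mortality aims have no time-to-event method in section 6, although censored cases are expected

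*Protocol article*

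**What the plan says.** **Aims.** Section 2.2.1 wants "the time course from the inciting insult to key endpoints such as severe disease", ECMO or death, and also to "analyze mortality patterns over a three-year follow-up period". Section 4.2 makes survival status at 36 months corrected age the primary follow-up outcome.

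**Censoring.** The Figure 1 legend states: "Outcome data, including censored cases, will be finalized in 2028 after completing follow-up through clinic visits or phone calls". Section 3.5 ends participation at death, at withdrawal of consent, or at transfer to a facility where follow-up is not feasible. Table 1 records the date of death, and the date and reason for loss.

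**Methods.** Section 6.1 lists two-group tests and then states: "Univariate logistic regression will be used to examine associations between NARDS and study outcomes". It continues: "Multivariable logistic regression will then be performed to identify independent predictors". Section 6.2 adds machine-learning classifiers for outcomes at 24 and 36 months. Sections 6.1 to 6.6 name no Kaplan-Meier, Cox, cumulative-incidence or competing-risk method.

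**Missing data.** Section 6.1 also states: "Missing data will be addressed primarily using multiple imputation by chained equations (MICE), assuming data are missing at random". Complete-case analysis, k-NN imputation and "inverse probability weighting to evaluate the robustness of findings to loss to follow-up" are sensitivity analyses. Exclusion criterion (4) in section 3.6.1 covers "cases with unavailable outcome data" without naming the outcome or the time point.

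**End of follow-up.** Section 3.1 closes the study on 31 December 2028. Section 3.6.2 plans recruitment over 2025-2028. Section 3.5 treats the cohort as complete only when every participant has had three years of follow-up.

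**The concern.** Two of the aims concern time to an event under incomplete follow-up, while the outcome regression in section 6.1 needs a known yes/no status and ignores time. Follow-up loss is also lopsided: an early death is known for good, whereas a living infant who moves away, or is recruited late, has no 36-month status. If that status is analysed as a binary variable, the treatment of the living infants without it drives the mortality estimate and can distort predictor effects. This touches the primary follow-up outcome and the comparison with the 12.6% and 17-24% mortality of earlier cohorts that motivates the study.

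**Working it through.** **The plan's own figure.** Section 3.6.2 needs 100 deaths at 12.6% mortality: 100 / 0.126 = 793.7, so 794. This reproduces. It concerns in-hospital mortality and does not bear on this point. The 12.6% is used below as the early death rate.

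**Case A: complete follow-up.** Every 36-month status is known, and a proportion or a logistic model at that horizon has no censoring bias. The time-course aim still lacks a method.

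**Case B: three years for all, ordinary loss.** Assumptions not in the article: a fraction *l* = 10%, 20% or 30% of survivors is lost, and all early deaths are known. Per 1,000 infants with no later deaths, the complete-case estimate is 126 / (126 + 874 × (1 − *l*)):

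- *l* = 10%: 126 / 912.6 = 13.8%
- *l* = 20%: 126 / 825.2 = 15.3%
- *l* = 30%: 126 / 737.8 = 17.1%

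The true value is 12.6%, so the excess is 1.2 to 4.5 points. If 5% of early survivors die later (true value 17.0%), the same calculation, with half of the later deaths among lost infants still observed, gives 18.3%, 19.9% and 21.9%. The excess is then 1.3 to 5.0 points.

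**Case C: data cut at 31 December 2028 (worst case).** Assumptions: 12.6% die early, then 1% per year; uniform accrual over *A* = 2, 3 or 4 years from January 2025; no other loss.

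- True 36-month mortality: 1 − 0.874 × 0.99³ = 15.2%.
- Only infants enrolled in the first year can reach 36 months, a share of 1/*A*. Corrected age makes it slightly smaller for preterm infants.
- Known survivors: 0.874 × 0.99³ / *A* = 0.848 / *A*.
- Observed deaths: 0.126 + 0.874 × 0.01 × mean follow-up, with follow-up capped at three years.
- Known-status estimate: observed deaths / (observed deaths + known survivors).

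| Accrual | Share able to reach 36 months | Mean follow-up (years) | Observed deaths | Known survivors | Known-status estimate |
|---|---|---|---|---|---|
| 2 years | 50% | 2.75 | 0.150 | 0.424 | 26% |
| 3 years | 33% | 2.33 | 0.146 | 0.283 | 34% |
| 4 years | 25% | 1.875 | 0.142 | 0.212 | 40% |

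Simulation with n = 1,000 gave the same three figures. Kaplan-Meier on the same data gave about 15.2% with a standard error of about 1.1 to 1.3 points. Using only infants enrolled early enough is unbiased but less precise, with a standard error of about 1.6 to 2.3 points.

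**Does the planned imputation repair Case C?** Not if a binary 36-month status is imputed. Filling in unknown statuses at the rate seen among known ones returns that same rate. Conditioning on survival of the early period helps but does not suffice. With four-year accrual, known-status early survivors show a death rate of 0.0163 / (0.0163 + 0.212) = 7.1%, against a true 1 − 0.99³ = 3.0%. The total becomes 0.126 + 0.874 × 0.071 = 18.8%, still above 15.2%. A valid correction conditions on being alive at last contact and on when that was, which is a time-to-event analysis.

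**Direction.** It is not fixed. Counting censored infants as alive gives 14.2% in the four-year version of Case C, about 1 point too low. Over a range of 0% to 5% later deaths, this handling errs by about 0 to −2 points.

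**The case against.** The strongest reply is that this is a journal article with the full analysis plan not shown, and that estimators and censoring rules usually belong there. No sentence assigns logistic regression to the time-course aim, and recording dates of death and loss is compatible with survival analysis. Part of this stands: the full plan may name such methods. But section 6.1 states a method for study outcomes, and section 6 goes down to k-NN imputation, instrumental variables and the R version. The method that it states does not fit these aims.

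It can also be said that medians with Mann-Whitney tests could describe time to event. They do so only among infants who reach the event, and they leave out censored infants and competing events.

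Four stronger readings are tempting, and the documents do not support them:

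- *Logistic regression is the only method.* Machine-learning models, multiple imputation and inverse probability weighting are also planned.
- *The estimates will be biased.* Survival at 36 months is a fixed-horizon outcome, for which logistic regression is valid when status is known. Under missing at random, imputation and weighting reduce bias from ordinary loss.
- *Mortality of 26-40% is what the plan will report.* That needs both a hard cut at end 2028, which section 3.5 contradicts, and an analysis of known-status infants, which section 6.1 makes a sensitivity analysis.
- *Exclusion (4) removes infants with partial follow-up.* It names no outcome or time point. The Figure 1 legend keeps censored cases, and section 4.2 reports loss to follow-up as an outcome.

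**Conclusion.** The point holds as a mismatch between aims and stated methods. The time-course and three-year mortality aims call for time-to-event methods, censoring is expected, and none is named. Logistic regression remains suitable for the 28-day composite and other outcomes with complete status.

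Bias is a risk whose size turns on the follow-up rule: none with complete follow-up; about +1 to +5 points for complete-case analysis with 10-30% loss among survivors; and 26-40% against about 15% in the worst case. The loss rates, the later mortality and uniform accrual are assumptions of this review; only the 12.6% comes from the article. The planned imputation and weighting lessen ordinary loss, but imputing a binary 36-month status does not handle administrative censoring.

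**What to change.** - In section 6.1, name Kaplan-Meier estimates with 95% confidence intervals and Cox regression for mortality to 36 months, censoring at last contact.
- For severe disease and ECMO, name cumulative incidence with death and discharge alive as competing events.
- Keep logistic regression for outcomes with complete status, such as the 28-day composite.
- State that exclusion (4) in section 3.6.1 does not remove infants with partial follow-up.
- Reconcile sections 3.1, 3.5 and 3.6.2 on the end of recruitment and of follow-up.

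The analysis changes cost some wording and standard R code. Dates of death and of loss are already collected (Table 1), so no new data are needed. Reconciling the dates requires a decision by the study team; if follow-up runs past 2028, the study period must be extended.
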